**Productivity**

*Socio-economic status*

Household socio-economic status will be measured using structured questionnaires measuring monthly household income and expenditures on health, education, clothing, food, housing and social activities. Data will also be collected on possession of assets such as televisions, radio, mobile phone, chair, cupboard, refrigerator, type of toilet, type of house walls, electricity and water source in the home and others. The Unmet basic needs index tool Core Welfare Indicator Questionnaire Survey (World Bank/Unicef) (CWIQ) [29] will be the basis for scoring poverty on the above listed factors.

*Demographic characteristics*

The PROMISE-EBF database already has multiple demographic characteristics including the age and date of birth for all the children. Data on age and sex will be reported for all family members as well as information on education.

*School involvement*

Each child’s school involvement will be assessed using information collected on the number of months enrolled in school and number of days attended in the past month/year. Children not yet in school will be assessed for school readiness based on findings from somatic and mental health examination.

**Moderators - Social emotional**

The mother’s or caretaker’s wellbeing will be addressed using a survey of health related quality

of life. In order to assess the environment in which the study children are being brought up and the relationship with the caregiver, a moderated African validated version of the HOME Screening Questionnaire will be used [30].

*Quality of relationships*

Caregivers will also be aided to complete the 34-item short form of The Parent Child Relationship

Inventory (PCRI) [135] in order for us to assess the caregiver-child relationship.

The PCRI yields four validated scores: 1) involvement; 2) quality of communication; 3) limit setting; and 4) autonomy.

*Relationships with peers*

These will be assessed using the Strengths and Difficulties Questionnaire (SDQ) as discussed in the behavioural and emotional sections above.

*Caregiver’s mental health and stress*

Caregivers will be requested and aided to complete the following interviews 1) the World Health Organization SRQ-20 [31], a self-reporting tool designed to assess the intensity of depressive symptoms experienced in the past 4 weeks; and 2) the Depression, Post-Traumatic Stress Disorder, and Substance Abuse modules from the Clinical Diagnostic Questionnaire (CDQ).

*Community*

The study group will address social networking, access to services and not-income generating activities and interests by identifying other actors in the study communities that might interfere with our exposure-outcome of interest.

We will be working in two low-income countries where resources are scarce, including stable power, clean water and sanitation, infrastructure and networking. We will assess around 800 child-mother (care-taker) pairs in their home-setting and a nearby facility in each country. It is evident that high-tech assessment, such as MRI, laboratory tests, etc., is not possible within the budget. Table 5 below shows maximum and minimum estimates of time for the different activities and assessments.

**Implementation**

As earlier mentioned, data collection will involve three steps: 1) a home-session, 2) clinical and

psychometric assessment session of the child, and 3) teacher structured interviews (when)

applicable.

*The home-session*

This will to a large extent be done by our data-collectors from the PROMISE EBF study. They will visit the households in the clusters assigned during the original data capturing. They will obtain informed consent and conduct most of the structured interviews addressed to the caretaker.

*Clinical and psychometric assessment session*

We will establish a number of study locations where we ensure a similar setup of our equipment. The equipment will move from one location to another – so we will use the same staff for the entire study population at each site. We imagine that a number of children from the same clusters will travel with one care-taker each to the study location work from test-to-test. The study locations will be school-buildings, administrative buildings or similar. We will try to avoid using health units knowing that many children have bad memories from those places. We will aim at making the place look safe and comforting.

Table 5: Maximum and minimum estimates of time for the different activities and assessments

| Activity |  | Estimated | Estimated |
| --- | --- | --- | --- |
| minimal time | maximal time |
| (minutes) | (minutes) |
| Home session | Introduction | 5 | 10 |
|  | Informed consent | 5 | 15 |
|  | Socio-demographic | 5 | 15 |
|  | Morbidity/hospitalization | 2 | 15 |
|  | Injuries | 2 | 15 |
|  | Productivity | 2 | 15 |
|  | Moderators/confounders | 10 | 20 |
|  | HOME-moderated | 5 | 10 |
|  | PCRI | 15 | 15 |
|  | SRQ-20 | 5 | 10 |
|  | SDQ | 10 | 20 |
|  | Closing/appointments | 5 | 10 |
| Summary, home |  | 71 | 170 |
|  |  |  |  |
| Assessment child | History, including 10 questions + | 5 | 10 |
|  | Clinical exam | 10 | 20 |
|  | Motor function | 20 | 40 |
|  | Anthropometry | 5 | 10 |
|  | Audiology | 5 | 15 |
|  | Vision | 5 | 15 |
|  | Cognitive function | 35 | 70 |
|  | Laboratory tests | 5 | 10 |
|  | Closing/appointments/referral | 10 | 20 |
| Summary, clinical |  | 95 | 200 |
|  |  |  |  |
| School contact | Teacher SDQ | 10 | 20 |
|  | Logistics/school | 5 | 10 |

**4.0 DATA COLLECTION AND MANAGEMENT**

Data will be collected on paper CRFs that will be entered in the study database for each site.

Previously collected data, as required, will be retrieved from the PROMISE EBF database.

**Statistical analysis**

The main exposure variable in this study will be having been randomized to an EBF peer

counselling cluster in the first six months of life. The main outcomes will be cognitive function and behavioural and emotional status, schooling, physical health and productivity. Analysis will be country specific and adjusted for clustering and site stratification.

We will estimate the association between the exposure and each of the continuous outcomes using linear regression. All these analyses will then be adjusted for baseline differences between groups (potential sources of confounding) in the original study such as socio-economic status and maternal education, in a multivariable linear regression. For categorical outcomes (e.g. food security) differences between the exposed and unexposed groups will be examined using chi- square tests. Prevalence ratios will be estimated using generalized linear models for the binomial family with a log link. Potential confounders will be adjusted for using multivariable regression models. All regression analyses will take into account the design effect (given the clustered nature of the original study design) and stratification.

The study team has established work packages for our secondary outcomes including scale-up, business packages and marketing of our intervention. Qualitative data for the secondary outcome on identifying solutions to potential barriers that limit scale up for peer counseling for EBF in the first six months of life was collected in the original study but not completely analyzed [32,33]. In this round, this data will be completely analyzed to meet this objective. To address the second secondary objective, health economists are already involved in the PROMISE EBF study and will address these issues in depth [34].

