**Project Summary**

The PROMISE Saving Brains (PROMISE-SB) study will include children born in the cohorts

established in Uganda and Burkina Faso between 2006 and 2008 for the PROMISE- EBF trial [1]. Using these cohorts, the PROMISE-SB study will give us a unique opportunity to assess whether EBF promotion enhances human capital formation and to assess mental health and cognitive function among 5-7 year old children in these two countries.

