**Mental health**

*Cognition and memory*

The team will use the Kaufman Assessment Battery for Children (K-ABC), the Luria-version which is to a large extent overlapping, but less language-dependent than the newer version KABC-II from 2004. Kaufman Assessment Battery for Children (K-ABC) was used and reliability checked for these contexts [27]. As a supplement Raven Progressive Matrices as a measure of intellectual function will be used. This has also been extensively used in Africa [28].

*Behavioural and emotional factors*

This study will apply the relatively short Strengths & Difficulties Questionnaire (SDQ) ([http://www.sdqinfo.com/)](http://www.sdqinfo.com/) for a gross assessment of behavioural and emotional factors. This is a screening tool with 25 items on 5 scales. When indicated, the child will be referred for further assessment to appropriate authorities. When applicable, we will administer the SDQ for teachers.

*Mental health co-morbidity assessment*

If any of the SDQ-scorings or home structured interviews and the assessment of the child give an indication for serious mental health challenges for the child, the study team will refer the child for follow-up investigation for potential diagnosis of: inattention and impulsiveness, autism-spectrum disorders, anxiety, depression, compulsive disorders, Tourette/tics, trauma and attachment difficulties. Counseling, therapy and treatment will be covered by the study team when feasible. Consent for information on diagnostic conclusions will be sought for.

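### Covariates for the continuous outcomes are chosen by observed baseline imbalance instead of a fixed prognostic set; no primary estimate is named, and the rule cannot reach age at assessment

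*Protocol*

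**What the plan says.** Protocol section 4.0, Statistical analysis, compares children by the arm to which their cluster was randomised. Continuous outcomes are first analysed by linear regression on arm. Then: "All these analyses will then be adjusted for baseline differences between groups (potential sources of confounding) in the original study", with two examples, "such as socio-economic status and maternal education, in a multivariable linear regression". For categorical outcomes the text says only: "Potential confounders will be adjusted for using multivariable regression models". Design factors are always included: "Analysis will be country specific and adjusted for clustering and site stratification". Several outcomes share top rank: "The main outcomes will be cognitive function and behavioural and emotional status, schooling, physical health and productivity".

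Nothing defines what counts as a baseline difference, closes the list of covariates, or says whether the unadjusted or the adjusted result is the main one.

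On age, the Project Summary says the study will "assess mental health and cognitive function among 5-7 year old children in these two countries". The Productivity section says the PROMISE-EBF database "already has multiple demographic characteristics including the age and date of birth for all the children". Under Clinical examination, the Movement ABC is to be reported against age-specific norms and anthropometry as z-scores. Under Mental health, the K-ABC is the cognitive test and "As a supplement Raven Progressive Matrices as a measure of intellectual function will be used"; neither is described as raw or age-standardised. Appendix I dates the neurodevelopmental and cognitive assessments April 2013 to May 2014. The Implementation section has the equipment moving between locations and children from the same cluster travelling in together.

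**The concern.** When arms are formed by randomisation, a covariate earns its place by predicting the outcome. A strong predictor that happens to be balanced still sharpens the estimate; an imbalanced variable unrelated to the outcome does nothing useful. A rule keyed to imbalance can keep the second and drop the first. It also makes the model depend on an undefined judgement about what counts as a difference, and with two estimates and no stated primary, the emphasis can be settled after both are seen.

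Age at assessment is a particular gap. It depends on the test date, so it is not a baseline variable of the 2006-2008 trial, and a rule about differences in that trial cannot pick it up even if the arms end up tested at different ages. At stake are the precision of the cognitive comparison and, if test dates happen to differ by arm, a difference in age showing up as a difference in score.

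**Working it through.** **The plan's own figures.** Appendix I sets a floor of 428 enrolled per country, from 404 plus 6%: 404 × 1.06 = 428.24, which reproduces. The 404 cannot be rebuilt, because no alpha, power, effect size, standard deviation (SD) or intracluster correlation is given. The loss therefore cannot be expressed against the plan's own power, and no power figure is claimed here.

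**Step 1: cost of selecting by imbalance.** From the protocol (Sites and sampling procedures): 24 clusters per country, 12 per arm. Assumed: no true effect; four independent cluster-level covariates jointly explaining R² = 30% or 60% of the variance of cluster means; a covariate enters if a t-test of the arms gives p below 0.05 or 0.20 (the protocol sets no threshold). Cluster means have unit variance. There were 8,000 runs per setting.

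| R² | Threshold | Type I error: fixed set | Selected | Either significant | SD of estimate: fixed set | Selected | Ratio |
|---|---|---|---|---|---|---|---|
| 30% | 0.05 | 4.9% | 4.3% | 5.4% | 0.378 | 0.404 | 1.07 |
| 60% | 0.05 | 5.0% | 3.6% | 5.1% | 0.288 | 0.386 | 1.34 |
| 30% | 0.20 | 4.7% | 3.1% | 5.4% | 0.374 | 0.388 | 1.04 |
| 60% | 0.20 | 5.1% | 2.3% | 6.1% | 0.288 | 0.348 | 1.21 |

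'Either significant' means reporting the unadjusted or the selected analysis if either reaches p < 0.05. The Monte Carlo standard error near 5% is √(0.05 × 0.95 / 8000) = 0.24 percentage points.

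Analytic check of the fixed set: SD = √[(2/12)(1 − R²)(21/17)], where 21/17 = 1 + 4/(24 − 2 − 4 − 1) is the price of fitting four covariates. This gives 0.380 at R² = 30% and 0.287 at 60%, in line with the table. Without adjustment it is √(2/12) = 0.408, against 0.404 to 0.409 simulated.

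Selection is conservative because a covariate is dropped only when it is balanced. It then disturbs the estimate little, but its variance stays in the residual and inflates the standard error.

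**Step 2: can the arms differ in age at testing?** April 2013 to May 2014 is 14 calendar months. As an illustrative extreme, suppose each cluster is tested on one date, uniform over the window and unrelated to arm. The SD of a cluster's date is 14/√12 = 4.04 months, and the SD of the arm difference is 4.04 × √(2/12) = 1.65 months. If every cluster's children were spread over the whole window, it would be close to zero. The protocol does not say how clusters will be ordered.

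**Step 3: what including age can gain.** If the score correlates r with age, adjustment removes r² of the individual-level variance: 9%, 25% or 49% at r = 0.3, 0.5 or 0.7 (assumed values), and about 0 if the score is already age-standardised. The protocol gives no r and does not state the score type.

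**The case against.** The strongest defence has four parts.

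- **The baseline data predate the outcomes.** The original trial ran in 2006-2008 and was published before this follow-up, so covariates chosen from its baseline do not depend on the follow-up results. This stands. A reader might infer that the rule inflates false positives; the simulation shows the opposite for selection alone, and only slight inflation when the significant analysis is the one reported. That inflation comes from the unstated primary estimate, not from the covariate rule.
- **Confounding is a fair worry here.** There are 12 clusters per arm, about 70% retracing is expected after several years, and Appendix I requires selection biases to be identified. The worry is fair, but the rule does not address it. Differences at original baseline do not show who was later lost, whereas a fixed prognostic set helps whichever way losses fall.
- **The list is open and an analysis plan may complete it.** The two covariates are only examples, and a full list is commonly left to a statistical analysis plan. So the absence of a list is not the point. The point is the selection principle the protocol does state, which a later plan following it would inherit.
- **Age may already be handled.** A reader might infer that the plan discards the strongest predictor of its main outcome. The documents do not support that: no predictor is ranked, there is no single main outcome, age is unnamed but not excluded, motor and growth measures are already age-referenced, and the cognitive scores may be. A reader might also infer an age spread of 4.3 to 8.4 years from the outer dates, but the lower end needs a December 2008 birth. If the 24-week visits ended within 2008, births stopped about mid-July and the youngest child would be about 4.7 years.

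**Conclusion.** The point holds in limited form. For the continuous outcomes, observed imbalance decides the covariates and no estimate is named as primary. On the assumed inputs this costs precision (SD of the estimate 4% to 34% larger than with a fixed set) and makes tests conservative (2.3% to 4.3%). Reporting whichever analysis is significant raises type I error only to between 5.1% and 6.1%. These sizes rest on the assumed number and strength of covariates and the assumed thresholds.

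The rule cannot select age at assessment, and the protocol does not say whether K-ABC and Raven scores are age-referenced. With test dates able to vary by cluster and 12 clusters per arm, a chance arm difference in age is plausible. What adjustment would recover runs from about nil to r² of the individual-level variance. It would be tempting to turn this into an equivalent number of extra children, but the documents supply neither r nor the score type, so no such figure is justified. This is an inexpensive improvement worth making, not a threat to the validity of the comparison.

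**What to change.** Replace the adjustment sentence in Statistical analysis so that:

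- the primary model for each continuous outcome, within country and allowing for clustering, includes the randomisation stratum where there is one (urban or rural residence in Uganda), age at assessment, sex, baseline household socio-economic status and maternal education;
- this set is fixed before follow-up outcomes are examined and kept whatever the observed imbalance;
- the unadjusted estimate is a sensitivity analysis;
- age may be left out where the score is already age-standardised, and the protocol states for K-ABC and Raven whether it is.

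The cost is a few sentences. Dates of birth are already held, socio-economic status and maternal education are named as original-trial variables, and sex is to be recorded. The only further item is the date of each child's test session. A fixed set is affordable with 24 clusters: in the simulation, even four cluster-level covariates kept type I error at 4.7% to 5.1%.

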**Sites and sampling procedures**

The original study (the PROMISE-EBF trial) conducted from 2006 to 2008 [1] took place in

Uganda, Burkina Faso, Zambia and South Africa. The current study will be conducted in Burkina Faso and Uganda because this is where the intervention had the largest documented impact. In Burkina Faso, the study site was located in rural Banfora, southwest of Burkina Faso. The Ugandan site was Mbale District, including urban Mbale Municipality and adjacent rural areas in Eastern Uganda. Clusters rather than individual mother-infant pairs were randomized to intervention or control to avoid potential spill-over between intervention and control arms and to improve the potential for scaling up this programme-relevant intervention. Clusters were mapped based on criteria of accessibility, population size, and health system characteristics and subsequently randomized by a central coordinating team into intervention or control arms. In total, 24 clusters (12 intervention and 12 control), with an average population size of 1000 inhabitants were selected in each country. In Burkina Faso and Uganda, all pregnant women in the study communities were approached for study participation and 99% consented to be screened for the study. In Uganda randomization was stratified on rural /urban residence reflecting the Uganda society: 20% in the urban and 80% in the rural areas. Overall, 895 pregnant women in Burkina Faso and 863 in Uganda were enrolled in the initial PROMISE-EBF trial. A recruitment interview was scheduled in the antenatal period or latest within one week after birth. Data collection visits were then scheduled at 3, 6, 12 and 24 weeks after birth. Inclusion in the study was a two-stage process involving first the pregnant woman (pre-inclusion) and then the infant (inclusion). Pregnant women intending to breastfeed were considered for study participation. The pre-inclusion criteria were that the woman resided in the selected cluster; was 7 months or visibly pregnant; had no plans to move in the forthcoming year; and provided informed consent. At the 3 week post-partum assessment a pre-included mother-infant pair was included if it was a single birth with no severe malformation which could interfere with breastfeeding. Exclusion criteria included severe psychological illness in the mother which could interfere with consent and study collaboration and intention to replacement feed. Unless a clear reason for non-participation in a scheduled visit was given, three attempts to see the mother-infant pair were made before a visit was considered missed. A recruited mother was revisited until the last scheduled visit irrespective of the number of missed visits; unless there was a clear reason for termination (e.g. declined further consent or moved). Data collection was done by trained independent data collectors in the mothers‟ homes. The data collectors were to the extent possible kept unaware of cluster allocation and were kept separate from peer counsellors and attended home visits on different days to peer counsellors to reduce information bias.

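### The chi-square tests named for categorical outcomes have no cluster adjustment and fall outside the regression-only design-effect sentence, which conflicts with the protocol's own commitment to adjust for clustering

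*Protocol*

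**What the plan says.** Under Sites and sampling procedures the protocol states: "Clusters rather than individual mother-infant pairs were randomized to intervention or control". It adds: "In total, 24 clusters (12 intervention and 12 control), with an average population size of 1000 inhabitants were selected in each country".

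The Statistical analysis section (under 4.0) makes four statements that bear on this point:

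- A general commitment near the start: "Analysis will be country specific and adjusted for clustering and site stratification".
- The test for categorical outcomes, with food security as the example: "differences between the exposed and unexposed groups will be examined using chi- square tests".
- The effect measure for such outcomes: "Prevalence ratios will be estimated using generalized linear models for the binomial family with a log link".
- The specific rule on clustering: "All regression analyses will take into account the design effect (given the clustered nature of the original study design) and stratification".

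The protocol states no ICC, no design effect and no significance level.

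**The concern.** A chi-square test in its usual form treats every child as an independent observation. Children here were allocated by cluster, so the variance of a difference between arms includes variation between clusters, which that test leaves out. It is the only hypothesis test that the section names for categorical outcomes. The one sentence that says how clustering enters the analysis is confined to regressions, and a chi-square test is not a regression. An analyst who follows the specific wording would run the unadjusted test, against the section's general commitment.

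Two things are at stake. First, chance differences between clusters could be read as effects of peer counselling, and the results are meant to inform scale-up. Second, the same outcome could be reported with a cluster-adjusted prevalence ratio and an unadjusted chi-square p-value that disagree, with no rule on which one governs.

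**Working it through.** **Inputs from the protocol**

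- Clusters per country: 24, allocated 12 and 12 (Sites and sampling procedures).
- Original enrolment (same section): "Overall, 895 pregnant women in Burkina Faso and 863 in Uganda were enrolled".
- Minimum number assessed per country: 404 (Appendix I, Activity 1.6).
- Follow-up target of 70%: 604 in Uganda and 626 in Burkina Faso (Appendix I, Activities 1.4 and 1.6).
- Planned assessments: around 800 per country (Moderators, under Community).

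**The plan's own figures first.** 0.70 × 863 = 604.1 and 0.70 × 895 = 626.5. The 604 and 626 are reproduced.

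**Assumptions, not in the protocol.** Significance level 5% two-sided; ICC from 0.01 to 0.10; equal cluster sizes; a binary outcome.

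**Formulas**

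- Mean cluster size: m = N / 24.
- Design effect: DE = 1 + (m − 1) × ICC.
- Actual type I error of an unadjusted chi-square test: 2 × [1 − Φ(1.96 / √DE)].

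**One case in full** (N = 604, ICC 0.05): m = 604 / 24 = 25.17. DE = 1 + 24.17 × 0.05 = 2.21. 1.96 / √2.21 = 1.32. The type I error is 18.7%, which is 3.7 times nominal.

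**All cases** (DE, then type I error)

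| N per country | m | ICC 0.01 | ICC 0.02 | ICC 0.05 | ICC 0.10 |
| --- | --- | --- | --- | --- | --- |
| 404 | 16.8 | 1.16, 6.9% | 1.32, 8.8% | 1.79, 14.3% | 2.58, 22.3% |
| 604 | 25.2 | 1.24, 7.9% | 1.48, 10.8% | 2.21, 18.7% | 3.42, 28.9% |
| 626 | 26.1 | 1.25, 8.0% | 1.50, 11.0% | 2.25, 19.2% | 3.51, 29.5% |
| 800 | 33.3 | 1.32, 8.8% | 1.65, 12.7% | 2.62, 22.6% | 4.23, 34.1% |

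Relative to 5%, the range is 6.9 / 5 = 1.4 to 34.1 / 5 = 6.8 times. At an ICC of 0.005 the inflation is only 1.2 to 1.4 times over the same sample sizes.

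**Check by simulation.** Beta-binomial data, 24 clusters, prevalence 30%, 20,000 runs per setting. With 25 children per cluster the unadjusted chi-square rejected in 8.0%, 10.2%, 18.6% and 28.3% of runs at ICC 0.01, 0.02, 0.05 and 0.10, in line with the formula. A t-test on the 12 against 12 cluster proportions rejected in 4.6% to 5.3% of runs in every setting tried (17, 25 or 33 per cluster; ICC 0 to 0.20).

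**The case against.** The strongest reply is that the section already commits the whole analysis to adjustment for clustering and exempts nothing. Cluster-adjusted chi-square tests exist, and the later sentence on regressions can be read as restating the general rule for models. The protocol nowhere says that the chi-square test will be unadjusted. This stands in part: a reader might infer a plan to ignore clustering, and the text does not support that. It does not remove the conflict, because the test as named has no adjustment and the operative sentence does not reach it.

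A reader might also infer that every categorical result is compromised. That goes too far. The prevalence ratios come from log-binomial models, which are regressions and so fall under the design-effect sentence. Continuous outcomes are assigned to linear regression and are likewise covered. Only the chi-square p-values are exposed.

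Nor can a fixed multiple of the nominal error be stated as fact, since it depends on an ICC that the protocol does not give. The protocol offers no evidence on how strongly food security, its only example, varies between clusters.

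Stratification does not add to the inflation. The protocol describes urban/rural stratification for Uganda only, and ignoring a balanced stratification factor generally makes a test conservative.

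Finally, the exact form of an adjusted test could be left to a statistical analysis plan. But the protocol did not leave the test open: it named one that, in its standard form, does not fit the design.

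**Conclusion.** The point holds as an internal inconsistency. The test named for categorical outcomes does not, as ordinarily run, respect the unit of randomisation, and the section's specific clustering rule omits it. The direction is certain for any positive ICC: the chi-square p-values would be too small. The size is conditional. At 5% two-sided and an ICC of 0.01 to 0.10, the type I error is about 7% to 22% at 404 children per country, 8% to 29% at 604, and 9% to 34% at 800, or about 1.4 to 6.8 times nominal. If the chi-square tests are in fact run in a cluster-adjusted form, as the general commitment would require, the inflation does not arise and only the wording needs correcting.

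**What to change.** Replace the chi-square sentence in the Statistical analysis section. Suggested wording: *Categorical outcomes will be compared between arms within each country by a cluster-adjusted chi-square test (for example Rao-Scott) or by a comparison of cluster-level proportions, accounting for the urban/rural stratum in Uganda.*

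Alternatively, drop the separate test and state that p-values for these outcomes come from the cluster-adjusted log-binomial models already planned. That also removes the risk of two conflicting results for one outcome. A categorical outcome with more than two levels would need the first option, or a stated way of making it binary.

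The cost is one sentence and no new data. The p-values will be larger than those from an unadjusted test, and some differences that such a test would call significant will no longer be so.
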